## Discussion

### Data monitoring

Considering the recent feasibility study that did not identify any significant complications with the RCB approach, which had a similar success rate compared with the coracoid ICB approach, and considering the relatively small number of patients per group, we will not have a formal data monitoring committee. For the same reason, no interim analysis will be conducted.

### Risk of bias

Unfortunately, the proposed methodology implies certain bias that would be hard to eliminate with the current research setup available in the participating centres. First of all, we will have selection bias because we will not be able to approach a consecutive series of patients, as personal resources are not sufficiently available, especially during the on-call hours, when recruitment depends on the anaesthesiologist and their “free” time for recruitment. Moreover, we will have reference centre bias because more anaesthesia providers are competent with RCB in Sherbrooke, and most of the enrolment will be in this university hospital.

For data collection, as it is not possible to double blind this trial for reasons previously described, so we will have performance bias. We might also include attention bias when asking patients if they have discomfort immediately after the plexus block and at 48 hours. However, this approach will be similar and neither group should influence one group more than the other. Finally, we might have therapeutic personality bias as in the consent form we mention our expectation of a shorter and less painful block with the RCB approach. However, we deemed it necessary to mention those facts because they are some of the implied reasons for the implementation of this trial.

For data analysis, we have two principal biases. First, we might have an “all is well in the literature” bias when using the Likert scale to evaluate needle visibility. This scale has been previously used in the similar studies; however, it has never been validated and results should thus be interpreted with caution. Unfortunately, no validated tools exist for this purpose. Furthermore, there might be detection bias even if the outcome assessor for the motor and sensory block is blinded to the procedure. To minimize this we will extend the chlorhexidine application to the two needle insertion points and two bandages will be applied even if no needle was inserted for one of them. However, blood leaking or soaking the bandage might inform the outcome assessor on the approach used.

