#### Intervention – concomitant care

Strict adherence to protocol will be mandatory to allow inclusion of patients. Thus, if any other needle or any other local anaesthetics or other volume/dose of local anaesthetics are used, the patient will be excluded from the analysis.

If the patient received more than 2 mg of midazolam (or equivalent dose of other sedative drug) during the procedure, the patient will be included only if he is still able to adequately collaborate during the evaluation of motor and sensory blockade.

This means that patients maintain adequate response to verbal commands and remain competent after the medication administration. In any circumstances, if the drugs given exceed the allowed sedation as mentioned in this protocol (fentanyl 1 μg/kg, propofol 50 μg/kg/min), the plexus block will be considered a failure.

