##### Secondary outcome measures

Imaging time: will be measured in minutes and corresponds to the time interval between contact of the US probe with the patient skin and the acquisition of a satisfactory image.Needling time: will also be measured in minutes, from the start of the skin wheal to the removal of the block needle from the tissues.Sensory loss at 10, 20 and 30 minutes: will be assessed in the territory of the radial (lateral aspect of the dorsum of the hand), median (volar aspect of the index), ulnar (volar aspect of the fifth finger), musculocutaneous (lateral aspect of the forearm), and medial cutaneous nerve of the forearm (medial aspect of the forearm) distributions using a 3-point score, where 0 = normal sensation, 1 = diminished sensation to pinpricks (hypoesthesia), and 2 = loss of sensation to pinpricks (analgesia). The sum of five scores on a maximum of 10 will be the sensory-loss final score. An independent, blinded, research assistant will complete the sensory assessment at 10, 20 and 30 minutes.Motor block at 10, 20 and 30 minutes: motor function will be tested (0 = normal strength, 1 = weakness, 2 = paralysis) for the radial (wrist extension), median (thumb-fifth finger opposition), ulnar (fifth finger abduction), and musculocutaneous (elbow flexion) nerves. The sum of the four scores on a maximum of 8 will be the motor block final score. An independent, blinded, research assistant will complete the motor assessment at 10, 20 and 30 minutes.Success of plexus block: success is a dichotomic variable answered by yes or no. Success is defined as the completion of surgery without the need for additional LA infiltration, intravenous narcotics, or general anaesthesia. However, light sedation is allowed if deemed necessary by the anaesthesiologist. Light sedation includes midazolam 1 to 4 mg intravenously, fentanyl up to 1mcg/kg. A minimum sensory score of 9/10 will be necessary to proceed to surgery without additional LA infiltration. Patients with an overall sensory score under 9/10 at 30 min will be offered general anaesthesia or supplemental blocks.Total anaesthesia time: is measured in minutes and defined as the sum of performance time and time to achieve a minimum sensory score of 9/10. It is the time for readiness for surgery.Number of block needle passes: is defined as a unit of 1, 2, 3, etc., and is the number of times the block needle will have to be realigned on the skin in order to achieve its final positioning goal under the axillary artery.Needle visualization: procedures will be videotaped and reviewed simultaneously after study completion by 2 independent anaesthesiologists skilled in US-guided regional anaesthesia using a 5-point Likert scale to rate needle visibility (1 = very poor, 2 = poor, 3 = fair, 4 = good, 5 = very good). Needle visibility will be evaluated twice. First, for RCB, assessment will be made when the needle tip is seen 1 cm after crossing the clavicle acoustic shadowing. For the coracoid ICB, the first assessment will be at a needle tip depth of 1 cm. The second needle visibility assessment will be immediately before the local anaesthetic injection, when the visibility is theoretically optimized.Needle angle: using the same videotape that we used for the evaluation of the needle visibility, we will note the angle between the needle and the upper side of the ultrasound image. It will be a continuous outcome ranging from 0 to 90 degrees.Neurostimulation use: neurostimulation is accepted if needed. However, its use other than for a safety sentinel (defined by <0.3 mA) will be recorded for subsequent analysis. It will be a dichotomous outcome.Pain during the procedure: immediately after block completion, patients will be asked to rate their discomfort associated with the procedure using a 10-cm visual analogue scale (0 = no pain, 10 = worst pain imaginable) by an independent and blinded outcome assessor.Early and late complications: the incidence of needle-induced paresthesia, vascular puncture, Horner syndrome, dyspnea, and symptoms of LA toxicity will be noted. All patients will be contacted 48 hours after surgery to ask for any delayed complications, such as dyspnea, paresthesia, weaknesses, pain at the puncture site or haematoma. Patients with complications will be followed up by our research group and a consultation in neurology may be sought.

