#### Blinding (masking)

In this trial, only the outcome assessor for the motor block and sensory block will be blinded. For obvious reasons, it is not possible to blind the anaesthesiologist performing the block. Moreover, the current setup at the included hospitals does not allow the blinding of the anaesthesiologist supervising the surgery. Thus, the anaesthesia team in the case of block failure will not be blinded. Patients will not be blinded either, as we opted not to fake a plexus block with another needle entry point for organizational reasons and to avoid patient discomfort. However, the primary outcome of performance time should not be affected by patient blinding. Considering that the anaesthesiologist will not be blinded, we did not think it necessary to blind the statistician as, even if blinded, the risk of contamination would be too high.

Discomfort during the procedure and the quality of the motor block and sensory block at 10, 20 and 30 minutes will be assessed by a blinded investigator. Another anaesthesiologist, resident or respiratory therapist will be in charge of evaluating sensory and motor function with pre-established indications to ensure competency. To reinforce blinding, chlorhexidine will be applied over the two theoretical needle entry points and two bandages will be applied.

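### Assessor masking for the sensory and motor scores can fail through a stained bandage or the patient's own words; the residual risk concerns secondary outcomes only and can be cheaply reduced

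*Protocol article*

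**What the plan says.** All references are to the protocol article.

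- **Who assesses.** Under Secondary outcome measures: "An independent, blinded, research assistant will complete the sensory assessment at 10, 20 and 30 minutes". The motor score has a parallel sentence.
- **How the assessor is masked.** Under Blinding (masking): "chlorhexidine will be applied over the two theoretical needle entry points and two bandages will be applied". The Risk of bias section repeats this.
- **What is conceded.** Risk of bias states that "there might be detection bias even if the outcome assessor for the motor and sensory block is blinded to the procedure", describes the two-site measure, and adds: "However, blood leaking or soaking the bandage might inform the outcome assessor on the approach used". The discussion of this bias ends there.
- **Patients.** Under Blinding (masking): "Patients will not be blinded either, as we opted not to fake a plexus block with another needle entry point for organizational reasons". Under Intervention – concomitant care, patients given more than 2 mg of midazolam are included only if they can still cooperate with testing, meaning that "patients maintain adequate response to verbal commands and remain competent after the medication administration".
- **What depends on the score.** Under Secondary outcome measures: "A minimum sensory score of 9/10 will be necessary to proceed to surgery without additional LA infiltration". Total anaesthesia time is performance time plus the time to reach that same score. A score below 9 at 30 minutes leads to an offer of general anaesthesia or supplemental blocks.

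**The concern.** The scores are graded judgements: normal, reduced or absent sensation in five territories, and normal strength, weakness or paralysis for four nerves. A borderline grade is where knowledge of the arm can influence a rating. The plan protects against this by hiding the puncture site, and itself says that the protection can fail.

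The patient is the less obvious route. The assessor meets a responsive patient at 10, 20 and 30 minutes, and that patient knows where the needle was placed. The Risk of bias section names the bandage but not the patient. The article also describes no record of whether masking held, so on its text a later report of blinded assessment could be neither supported nor questioned.

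At stake are the between-arm comparisons of sensory and motor score and of total anaesthesia time, all tested for superiority, and the proportion of patients reaching 9/10 by 30 minutes.

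**Working it through.** The plan states no figure for masking, so there is none to reproduce. Its 49 patients per group serve below only as a denominator.

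**1. Which outcomes pass through this assessor?**
- Sensory and motor score: directly.
- Total anaesthesia time: through the time to reach 9/10.
- The 30-minute offer of general anaesthesia or supplemental blocks: through the sensory score.
- Performance time (primary): no. It is imaging time plus needling time, taken with a chronometer, and ends when the needle is withdrawn, before the first score at 10 minutes. The Sample size inputs are all performance times, so required numbers and power do not change.

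**2. Effect of one tipped grade.**
- Maximum sensory score: 5 territories × 2 = 10; threshold 9. One grade in one territory takes a patient from 8 to 9.
- If onset is read from the 10-, 20- and 30-minute checks (my assumption), and the patient would otherwise have reached 9 at the next check, a tip at 10 or 20 minutes moves that patient's onset by 10 minutes.
- Effect on the arm mean: 10/49 = 0.20 min, about 12 s.
- Effect of one tip at 30 minutes on the share reaching 9/10: 1/49 = 2.0 percentage points.
- If five patients were tipped the same way (assumed): 5 × 10/49 = 1.02 min, or 5/49 = 10.2 points.

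**3. Illustration of the effect on the tests.** The sensory score has 11 possible values (0–10) and the motor score 9 (0–8). Both exceed the plan's limit of 8 categories, so means and, where suitable, a *t* test apply. Let u be the share of assessments unmasked and s the rating shift in SD units, all in one direction; both are assumed. The spurious difference is b = u × s and the noncentrality is b/√(2/n). With n = 49, √(2/49) = 0.202. For a two-sided 5% test with no true difference:

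| u | s | b | b/0.202 | type I error |
|---|---|---|---|---|
| 10% | 0.5 | 0.05 | 0.25 | 0.057 |
| 25% | 0.5 | 0.125 | 0.62 | 0.094 |
| 50% | 0.5 | 0.25 | 1.24 | 0.23 |
| 100% | 0.5 | 0.50 | 2.48 | 0.69 |

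The first row suggests that occasional bandage leakage alone would matter little. The lower rows show that frequent disclosure could matter, if it also shifted the ratings. The documents do not say which row applies.

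**4. Direction.** Under Allocation: sequence generation, one centre mostly uses the retroclavicular and the other the infraclavicular approach. Assessors at the two sites might lean opposite ways. Most enrolment is expected in Sherbrooke, so any offset would be partial, but no net direction follows.

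**The case against.** The strongest reply is that the authors saw this risk, took a reasonable countermeasure and disclosed what remained. They also describe the trial's biases as hard to eliminate with their setup. That stands: nothing is misstated, and the risk was neither overlooked nor left untreated. Disclosure does not reduce it, however, and a better cover is available.

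A second reply is that a condensed article need not print assessor instructions. A non-disclosure request or a guess question may sit in the full protocol or the data form. That also stands, so their absence here is weak evidence. The point rests on what is stated: a masking method that can fail, and unblinded patients.

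Three stronger readings are tempting but unsupported:

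- **That these are the only masked data.** One sentence under Blinding (masking) says so, but the next paragraph and Secondary outcome measures also give procedural discomfort a blinded assessor. That masking is weak, since the unblinded patient supplies the rating, but the claim cannot be made.
- **That the person who times the block or holds the envelopes also scores it.** Research assistants appear in all three roles, and the scorer is elsewhere an anaesthesiologist, resident or respiratory therapist. The scorer is nevertheless called independent and blinded, so a shared role is not shown.
- **That the non-inferiority result is compromised.** Step 1 shows that it is not.

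**Conclusion.** The point holds as a cheap improvement to an acknowledged limitation, not as an error in the plan. A residual, reducible detection-bias risk remains for the sensory and motor scores, total anaesthesia time and the 9/10 rule. Its size and direction cannot be derived from the documents: the per-patient figures assume a score of exactly 8 at the relevant check, and the type I error figures rest entirely on assumed unmasking rates and rating shifts.

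A reader might infer that the gap can be closed. It cannot while patients know their approach: they may still speak, and their own answers to pinprick are part of the score. Block success would not become masked either, because the team handling block failure is declared unblinded.

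**What to change.** In Blinding (masking), add:

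1. An identical opaque cover is placed over both dressings before the assessor enters.
2. Patients and the block team are asked not to tell the assessor which approach was used.
3. After the 30-minute scores are entered, the assessor records which approach they believe was used, and whether it was seen or disclosed.

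Report these guesses by arm. Keep the comparison of all patients as the main analysis. Any analysis that leaves out unmasked assessments should be descriptive only: unmasking happens after randomization and may differ by arm, so excluding on it can itself introduce bias.

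The cost is one cover and one form line per patient and a sentence to patients and staff, with no change to sample size. About one quarter of the calculated sample had been recruited when the article was submitted. Patients assessed before the change fall under the masking as now described, so the report should state when it took effect.

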### Harms

Potential harms are mentioned to the patient as standard before any regional anaesthesia, including risk of pneumothorax, transient or permanent nerve injury, vascular puncture, infections, Horner syndrome or failed plexus block. This practice will be maintained throughout this trial. Any adverse effects or complications will be compiled in the data collection form, but we do not expect to have enough power to find any significant differences. In the feasibility study, no significant or permanent harms were inflicted on the patients with the experimental method. Moreover, we expect better visibility with the RCB approach, which could be associated with reduced risk of complications.

If important harms or concerns about patient safety are noted, we will report to the research group and ethics committee for evaluation on the continuation of the trial. We will also act accordingly in seeking appropriate medical attention if deemed necessary.

### Auditing

No auditing is planned. If considered necessary by the research members, auditing on the quality of the data gathering might be conducted for the specific anaesthesiologist with whom atypical or incomplete data are obtained.

### Confidentiality

Confidentiality is a priority in this project to ensure non-maleficence. Every patient will have a corresponding number. This corresponding number will be linked to the patient file number in an Excel file that will be kept on a locked computer in a locked room within the hospital. No other computer will contain the corresponding numbers with the file numbers. Patient file number and the corresponding number will be inscribed directly on the locked computer and will never transit via the Internet or email. Only the research members may access the locked computer.

Data collected will be in another Excel file that will contain only the corresponding number. No computer will ever have both the Excel files. Thus, we will ensure that no computer loss will allow patient identity to be associated with the collected data. Only the research members and statisticians may have access to the collected data. Videos of the ultrasound machine screen will be sent to the principal investigator centre via a password-protected Dropbox® file and they will be stored in the locked computer with the rest of the patient information as soon as possible. Videos will only contain the ultrasound images and it will not be possible to recognize patients by watching those videos. The name of the video will be the patient number.

## Trial status

At the time of manuscript submission, the recruitment of the patients has started and is ongoing. We have recruited one fourth of the calculated sample size.

## Abbreviations

BMI: Body mass index
ICB: Infraclavicular
OR: Operating room
RA: Regional anaesthesia
RCB: Retroclavicular
USG: Ultrasound-guided
